## Abstract

**Background:**

The Melanoma Genomics Managing Your Risk Study is a randomised controlled trial that aims to evaluate the efficacy of providing information on personal genomic risk of melanoma in reducing ultraviolet radiation (UV) exposure, stratified by traditional risk group (low or high phenotypic risk) in the general population. The primary outcome is objectively measured total daily Standard Erythemal Doses at 12 months. Secondary outcomes include UV exposure at specific time periods, self-reported sun protection and skin-examination behaviours, psychosocial outcomes, and ethical considerations surrounding offering genomic testing at a population level. A within-trial and modelled economic evaluation will be undertaken from an Australian health system perspective to assess the cost-effectiveness of the intervention.

**Objective:**

To publish the pre-determined statistical analysis plan (SAP) before database lock and the start of analysis.

**Methods:**

This SAP describes the data synthesis, analysis principles and statistical procedures for analysing the outcomes from this trial. The SAP was approved after closure of recruitment and before completion of patient follow-up. It outlines the planned primary analyses and a range of subgroup and sensitivity analyses. Health economic outcomes are not included in this plan but will be analysed separately. The SAP will be adhered to for the final data analysis of this trial to avoid potential analysis bias that may arise from knowledge of the outcome data.

**Results:**

This SAP is consistent with best practice and should enable transparent reporting.

**Conclusion:**

This SAP has been developed for the Melanoma Genomics Managing Your Risk Study and will be followed to ensure high-quality standards of internal validity and to minimise analysis bias.

**Trial registration:**

Prospectively registered with the Australian New Zealand Clinical Trials Registry, ID: ACTR N12617000691347. Registered on 15 May 2017.

## Introduction

### Preface

Melanoma is a serious form of skin cancer associated with significant morbidity and mortality but is highly preventable through individual behaviour change [1, 2]. Reduced sun exposure and improved primary prevention behaviours (i.e. sun protection) could prevent over 80% of melanoma diagnoses [3]. However, in high-incidence countries, such as Australia, preventive behaviours remain sub-optimal and there is a need to further improve melanoma prevention strategies aimed at the broader population [4].

Genomic risk information, based on multiple common genetic variants associated with elevated risk, could be integrated into improved melanoma prevention and early detection strategies [5, 6]. Social and health behaviour theory suggests that personal genomic risk information, alongside support and education on prevention and early detection, may be more effective in motivating behaviour change than ‘one size fits all’ standard approaches [7–9]. But the research evidence on genomic risk interventions in healthy participants is limited by small sample sizes and a high risk of bias, and few of these studies have focussed on melanoma prevention behaviours [10, 11].

The *Melanoma Genomics Managing Your Risk Study*, an innovative randomised controlled trial (RCT), aims to establish whether providing personal genomic risk information modifies preventive behaviours, compared to receiving standard prevention advice [12]. A pilot RCT demonstrating feasibility and acceptability, and the trial protocol, were previously published [12, 13]. The study was prospectively registered (ANCTRN 12615000356561). The trial completed the target accrual in February 2019, and all participants will be followed up for 12 months. The statistical analysis plan (SAP) reported here is Version 1.1, signed off by the principle investigator and study statisticians on 24 April 2020. The corresponding protocol has been published elsewhere [12]. The reporting of this SAP is in accordance with the guidelines for the content of SAPs in clinical trials [14].

### Purpose of the study and analyses

To evaluate the impact of personal genomic risk of melanoma information on motivating skin cancer prevention behaviours, and on broader social, psychological, ethical and economic outcomes.

## Study aims and outcome measures

### Aims

#### Primary

The primary aim is to evaluate the efficacy of providing information on personal genomic risk of melanoma in reducing ultraviolet radiation (UV) exposure at 12 months, stratified by traditional risk group (low or high phenotypic risk) in the general population.

#### Secondary

The secondary aims are to evaluate:
The intervention’s effect at 12 months on:
time-specific UV exposureself-reported UV exposuresun-protection behavioursskin examinationsThe effect on other behavioural outcomes including:
tanningsunburn frequencyhypothesised mediators of behaviour changePsychological outcomes, including skin cancer-related worry and distressThe intervention’s effect on short-term outcomes at 1 monthThe impact of personal genomic risk categories (lower than average, average or higher than average) on primary and secondary outcomes in the intervention arm aloneThe experience of the intervention, psychological impact of undergoing genomic testing and receiving results, and communication with others about the results

Sub-studies beyond the scope of this SAP:
7.Qualitative sub-study assessing ethical considerations surrounding offering genomic testing at a population level, and psychosocial issues arising from the study processes that may affect wider implementation8.Cost-effectiveness analysis of the intervention at 12 months and in the longer term from an Australian health-system perspective (refer to the Health Economics Analysis Plan (HEAP [15]) for more details)9.Correlates of sun exposure, sun protection and skin examination behaviours, using baseline data

### Outcome measures

#### Primary outcome measure

The primary outcome for this study is total daily Standard Erythemal Doses (SEDs) measured 12 months after the baseline assessment (baseline questionnaire and UV dosimeter). A SED is an objective measure of UV exposure, measured using a time-stamped electronic dosimeter badge, mounted in light-weight, custom-made wristbands attached to the left wrist (similar to wearing a watch) during daylight hours [16]. UV dosimetry is the gold standard for assessing personal UV exposure [17, 18]. UV dosimeters will be worn by all participants for 10 days at baseline, and again 12 months after baseline. A subgroup of ~ 240 participants will also wear a UV dosimeter 1 month after receipt of the booklet/s. Total daily SEDs will be calculated as the weighted average of the average daily weekday and weekend SEDs (i.e. (weekday× 5 + weekend× 2)/7). SED values will be log-transformed for all analyses.

#### Secondary outcome measures

Time-specific UV exposure captured from the time-stamped UV dosimeters. This will be calculated as the weighted average within given time points: morning, peak and afternoon periods will be defined respectively as ‘6 a.m. to 10 a.m., 10 a.m. to 2 p.m. and 2 p.m. to 8 p.m.’ (without daylight savings).

Self-reported UV exposure on weekdays and weekends assessed using questionnaire items: *Thinking about the past month, please tell us the times of day as well as the usual length of time that you spent outside between 7 am and 6 pm on a typical weekday and weekend.* Length of time is collected in 15 min intervals (0, < 15, 15–29, 30–44, 45–60 min), and will be recoded to the mid-point of the respective exposure times. Total weekday and weekend sun exposure will be calculated as the sum of mid-point exposure times. Self-reported UV exposure will be calculated as the weighted average of the average weekday and weekend self-reported UV exposure (i.e. (weekday× 5 + weekend× 2)/7).

Sun-protection behaviours [19] assessed individually and summarised as a Sun Protection Habits Index, which is calculated as the mean of six protective behaviours scored on a 4-point Likert scale (1 = never or rarely, 2 = sometimes, 3 = often, 4 = always): *During the past month, when outside, how often did you…*Wear sunscreen?Wear a shirt with sleeves that cover your shoulders?Wear a hat?Stay in the shade or under an umbrella?Wear sunglasses?Limit your time in the sun during midday hours?

Sunscreen use is assessed using an item: *Have you used sunscreen in the past month?* (yes/no). If participants respond ‘yes’ they are asked the following items:
*Was this usually a high-protection sunscreen (SPF 30 or more)?* (yes/no)*How often on average have you used sunscreen in the past month?* (less than once a week, 1–2 days a week, 3–5 days a week, 6–7 days a week)*On days that you have used sunscreen in the past month, how often did you apply it?* (open response restricted to numbers)Did you usually apply sunscreen (select one of the following): to all parts of your body exposed to the sun OR only to parts of your body that are prone to sunburn.

Hat wear is assessed an additional item: *Please select the option which is most similar to your usual headwear when in the sun in the past month.* Response options are: no headwear, beanie, cap, legionnaire’s hat, bucket hat, wide-brimmed hat, veil/burka.

Whole-body skin examinations, performed on oneself or by a partner or (in a separate question) by a health professional [19, 20] will be dichotomised as ‘yes’ vs. ‘no’. If the response in the 12-month questionnaire to either:
*In the past 12 months, have you, your partner, friend or family member checked at least some of your skin for any suspicious spots that might be skin cancer?* or*In the past 12 months, have you had a health professional (e.g. a physician, specialist or nurse) check at least some of your skin for any suspicious spots that might be skin cancer?*is ‘yes’ then the extent of skin check (1 = all or nearly all of your body, 2 = part of your body, 3 = checking a specific mole or spot) is assessed. If either the self-check or health professional check response is ‘All or nearly all of your body’ then whole skin examinations will be coded as 1: yes. All other responses (including those that have no skin checks) will be coded as 0: no.

Intentional tanning frequency will be measured on a 5-point Likert scale (1 = never, 2 = rarely, 3 = sometimes; 4 = often, 5 = always) in response to the question: *In the past month, how often do you spend time in the sun in order to get a tan?*

Sunburn frequency over the previous month [20] will be collected as ‘0’, ‘1’, ‘2’, or ‘3 or more times’ in response to the question: *In the past month, how many times did you have a red or painful sunburn that lasted a day or more*? This will also be categorised as ‘any’ versus ‘none’.

Hypothesised mediators of behaviour change will be measured by the following items:

Perceived severity of melanoma [21]: *To what extent do you agree or disagree with the following?*I believe that melanoma is easy to cureI believe that melanoma can have very severe consequencesGetting melanoma would be a big health threat for me

A mean score will be derived from response options on a 5-point Likert scale: 1 = strongly disagree, 2 = disagree, 3 = neither agree nor disagree, 4 = agree, 5 = strongly agree.

Perceived risk of melanoma [22]:

*Write a number between 0 and 100 (where 0 means no chance and 100 means absolute certainty) to show what you think the chance is that you will develop melanoma during your remaining lifetime.*

*How confident are you in the number you wrote above?* Response options are on a 5-point Likert scale: 1 = not at all confident, 2 = slightly confident, 3 = somewhat confident, 4 = quite confident, 5 = very confident [23].

*Compared to the average person of your sex and age, what do you think the chance is that you will develop melanoma in your lifetime?* Response options are on a 5-point Likert scale: 1 = much below average, 2 = somewhat below average, 3 = average, 4 = above average, 5 = much above average.

Confidence in identifying melanoma [21]; *How confident are you in your ability to identify melanoma?* Response options are on a 5-point Likert scale: 1 = not at all confident, 2 = slightly confident, 3 = somewhat confident, 4 = quite confident, 5 = very confident.

Perceived effectiveness of specific sun-protection behaviours in reducing personal melanoma risk [24]: *For me, (using sunscreen/wearing protective clothing (such as long sleeves, long pants, hat)/avoiding sun exposure during midday hours) is (or would be) effective in reducing my risk of developing melanoma.* Response options for these three items are on a 5-point Likert scale: 1 = not at all effective, 2 = a little effective, 3 = somewhat effective, 4 = moderately effective, 5 = very effective.

Perceived importance of protective behaviours: *How important are these activities?** Limiting sun exposure in the middle of the day; Wearing long-sleeved shirts; Wearing long pants; Wearing a wide-brimmed hat; Using sunscreen of SPF 30 or higher; Asking your physician to conduct a skin examination; Checking your own skin for suspicious spots/moles; and Staying in the shade.* Response options are on a 4-point Likert scale: 1 = not at all important, 2 = not very important, 3 = somewhat important, 4 = extremely important.

Perceived capability of performing protective behaviours: *How capable do you feel that you can do these things well, whether or not you intend to do them?* (the same eight protective behaviours listed for perceived importance of protective behaviours above). Response options are on a 4-point Likert scale: 1 = not at all capable, 2 = not very capable, 3 = somewhat capable, 4 = extremely capable.

Social norms about skin examinations and sun protection [21]: *How many (adult members of your family/friends) check their own skin, or have their skin checked by someone else at least every 2 years? How many of your (family members/friends) do you think regularly take precautions in the sun (such as using sunscreen, wearing protective clothing, avoiding sun during midday hours)?* Response options are: 1 = none, 2 = some, 3 = half, 4 = most, 5 = all, 6 = I don’t know.

Skin Self-Examination Attitude Scale (SSEAS) [25]: *To what extent do you agree with the following statements:*It is important to check my skin for skin cancer even if I have no symptomsChecking my skin regularly is a priority for meI think I could find something suspicious on my skin if it was thereIf I saw something suspicious on my skin, I’d go to the physician straight awayI am confident in a physician’s ability to diagnose skin cancerI am confident that I can take up examining my own skin even if I have not looked at my skin the past few monthsI am able to examine my own skin regularly, even if I have no one to help meIf I regularly examine my skin, then I am helping to look after my own health

Response options are on a 5-point Likert scale: 0 = strongly disagree, 1 = disagree, 2 = unsure, 3 = agree, 4 = strongly agree. Responses to each item will be summated to generate a total score that can range between 0 and 40.

Tanning attitudes (pro-tan score) [26]: *To what extent do you agree with the following statements:*I feel more healthy with a suntanA suntan makes me feel better about myselfA suntan makes me feel more attractive to othersThis summer I intend to sunbathe regularly to get a suntanMost of my close family think that a suntan is a good thingMost of my friends think a suntan is a good thingA suntan protects you against melanoma and other skin cancers

Response options are on a 5-point Likert scale: 1 = strongly disagree, 2 = disagree, 3 = neither agree nor disagree, 4 = agree, 5 = strongly agree. Responses to the seven items will be summated, giving a total score between 7 and 35; those with a total score of 7–14 will be classified as ‘anti-tan’.

Anxiety about skin-examinations [25]: *I think checking my skin would make me anxious.* Response options are on a 5-point Likert scale: 1 = strongly disagree, 2 = disagree, 3 = unsure, 4 = agree, 5 = strongly agree.

Perceived control over developing melanoma [24]; *Overall, how much personal control do you feel you have over (whether you develop melanoma in the future?*/*detecting a future melanoma early in its development?)* Response options are on a 5-point Likert scale: 1 = no control, 2 = not much control, 3 = some control, 4 = moderate control, 5 = a lot of control.

Family communication: *In the past month, how frequently have you discussed with your family: using sunscreen; wearing protective clothing (such as long sleeves, long pants, hat); avoiding sun exposure during midday hours; getting a skin check by a health professional (e.g. general practitioner (GP) or dermatologist); doing personal skin checks; spending time in the sun to get a tan?* Response options are on a 5-point Likert scale: 1 = not at all, 2 = a little, 3 = sometimes, 4 = quite a bit, 5 = a lot.

Vitamin D knowledge: *Do you believe that if you always protect all your skin from the sun, you are in danger of not getting enough Vitamin D?* Response options are: yes, no, I don’t know.

Health professional advice about sun protection and skin examinations: *In the past 12 months, has a health professional provided you with information or advice about sun protection, or how to check your skin for early signs of melanoma?* Response options are: yes, no.

Barriers to sun protection: *If you do not regularly use sunscreen, can you tell us the reason for this? If you do not regularly wear protective clothing (such as long sleeves, long pants, hat), can you tell us the reason for this? If you do not regularly limit your time in the sun during midday hours, can you tell us the reason for this?* Each of these items have a free-text response field and will be analysed using content and thematic analysis.

Other potential mediators include items on: the importance of personal health in achieving life goals [27] (assessed using a 5-point Likert scale); perceived general health [28] (assessed using a 5-point Likert scale); frequency of information-seeking related to skin cancer, genetics and genetic counselling; use of the study website; and use of applications (apps) to assist with managing sun protection or skin examinations.

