Additional MICRA items that are assessed separately to the subscales include: Feeling regret about getting my risk information; and Understanding clearly my choices for melanoma prevention or early detection. In addition, if the participant has a child(ren), two additional items are assessed: Worrying about the possibility of my child(ren) getting melanoma; Feeling guilty about possibly passing on the melanoma risk to my child(ren). If the participant has cancer, or has had it in the past, the following items are also assessed: Feeling that my genetic risk information has made it harder to cope with my cancer; and Feeling that my genetic risk information has made it easier to cope with my cancer. The responses are scored as 0 for ‘never’, 1 for ‘rarely’, 3 for ‘sometimes’ and 5 for ‘often’ for the distress and uncertainty MICRA subscale items; and as 5 for ‘never’, 3 for ‘rarely’, 1 for ‘sometimes’ and 0 for ‘often’ for the positive experiences subscale items. The scores will be summated for each subscale, and the three subscales also summated to give a total score. Higher values of the MICRA score are related to increased experiences of distress. The questionnaire items for the additional MICRA items will be scored the same way as the distress and uncertainty subscales, with the possible range of 0–5 when there is one item, and 0–10 when there are two items.

The Genetic Counselling Satisfaction Survey (GCSS) [32]: *To what extent do you agree with the following statements?*I felt I could talk about my reaction to my risk information with the genetic counsellorThe genetic counsellor helped me to understand my risk information and make decisions about my health careI felt better about my health after talking to the genetic counsellorThe length of the phone call was appropriateThe genetic counsellor was truly concerned about my well beingTalking to the genetic counsellor was valuable to meUnderstanding of genetic risk information, and amount read by participants

Response options are on a 5-point Likert scale: 1 = strongly disagree, 2 = disagree somewhat, 3 = uncertain, 4 = agree somewhat, 5 = agree strongly.
Recall of personal genetic risk categoryCommunication of result with family, friends and health professionalsMotivations and barriers to family communication about genetic risk [33]Satisfaction, understanding and amount read of the personal genetic risk booklet

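### Perceived severity and the MICRA coping pair combine oppositely worded items without aligning them, which weakens the first score and makes the second uninterpretable

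*SAP article*

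**What the plan says.** **Perceived severity** (SAP article, Secondary outcome measures, hypothesised mediators). Three items share one agreement key: melanoma is easy to cure, melanoma can have very severe consequences, and melanoma would be a big threat to my health. The scoring rule is "A mean score will be derived from response options on a 5-point Likert scale: 1 = strongly disagree", continuing to 5 for strong agreement. Nothing is said about reversing an item.

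**Additional MICRA items** (Psychological outcomes, intervention arm only). These are assessed apart from the three subscales. One set is "Feeling regret about getting my risk information; and Understanding clearly my choices for melanoma prevention or early detection". A second, for parents, covers worry about and guilt towards children. A third, for participants with current or past cancer, asks how the information affected coping. Its negative item is "Feeling that my genetic risk information has made it harder to cope with my cancer". Its positive counterpart asks whether coping became easier. The rule for all of them is "The questionnaire items for the additional MICRA items will be scored the same way as the distress and uncertainty subscales". The resulting scores are then given a range of 0 to 5 for a single item and 0 to 10 for a pair. The distress and uncertainty key is 0, 1, 3, 5 from never to often.

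**SSEAS** (Secondary outcome measures). Eight statements are listed, each scored 0 to 4, and the responses are "summated to generate a total score that can range between 0 and 40".

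**Reversal elsewhere.** Under Psychological outcomes the article reverse-codes MHI-5 items (c) and (e), and gives the MICRA positive-experiences items the key 5, 3, 1, 0.

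**The concern.** A mean or sum of items measures a construct only if all items point the same way. In the severity scale one item of three points the other way. In the coping pair one of two does, and there the text prescribes the shared direction instead of merely leaving it open.

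Hypothesised mediators and the psychological impact of testing are both named in the secondary aims. If the severity rule is programmed literally, a small or null intervention effect on perceived severity could be produced by the scoring. The coping score could not tell a participant harmed by the information from one helped by it.

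The planned quality control would not necessarily catch this. Under Technical details, independent reproduction covers the primary analyses, with other tables selected at random, and code that faithfully follows a misdirected rule would pass a check against the plan.

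**Working it through.** **1. Stated ranges.** Two MICRA items keyed 0/1/3/5 sum to between 0 + 0 = 0 and 5 + 5 = 10. This reproduces the stated 0–10 and shows that two-item sets are summed. The pro-tan range (7 × 1 = 7 to 7 × 5 = 35) and the MHI-5 raw range (5 × 1 = 5 to 5 × 6 = 30) also reproduce. The SSEAS range does not: 8 × 4 = 32, against 40.

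**2. Severity, consistent respondents.** Someone at severity level k (1 to 5) answers 6 − k on easy to cure and k on each of the other two.

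| k | Answers | Mean as written, (6 + k)/3 | Mean with item 1 reversed |
|---|---|---|---|
| 1 | 5, 1, 1 | 2.33 | 1 |
| 2 | 4, 2, 2 | 2.67 | 2 |
| 3 | 3, 3, 3 | 3.00 | 3 |
| 4 | 2, 4, 4 | 3.33 | 4 |
| 5 | 1, 5, 5 | 3.67 | 5 |

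The order is kept, and the span shrinks from 4 points to 1.33. If severity rises by d on every item, the written mean moves by (−d + d + d)/3 = d/3.

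**3. Severity, standardised effect.** The raw loss overstates the loss of power, because the noise changes too. Assume equal item SDs and a common inter-item correlation ρ after alignment. The variance of the sum is then proportional to 3 + 6ρ when aligned and 3 − 2ρ as written, so

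share of standardised effect kept = (1/3) × √[(3 + 6ρ)/(3 − 2ρ)].

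The article gives no ρ, so a range is shown. The power column starts from a comparison with 80% power at 189 per arm, which is the Sample size section's 378 per phenotype group split evenly between the arms.

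| ρ (assumed) | Share of effect kept | Power instead of 80% |
|---|---|---|
| 0 | 33% | 15% |
| 0.3 | 47% | 26% |
| 0.5 | 58% | 37% |
| 0.7 | 71% | 51% |

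**4. Coping pair.** Mirror-image answers, with harder first and easier second:

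| Answers | As written | Easier keyed 5/3/1/0 |
|---|---|---|
| often, never | 5 + 0 = 5 | 5 + 5 = 10 |
| sometimes, rarely | 3 + 1 = 4 | 3 + 3 = 6 |
| rarely, sometimes | 1 + 3 = 4 | 1 + 1 = 2 |
| never, often | 0 + 5 = 5 | 0 + 0 = 0 |

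As written, each experience scores the same as its opposite. Aligned, the scores run from 0 to 10 in order of harm.

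**5. The other additional MICRA items.** Worry and guilt about children point the same way, so that pair is sound. Regret and clear understanding point in opposite directions, but no sum of the two is stated. The parent and cancer sets each have two items, so the one-item range of 0–5 would apply to nothing unless regret and understanding are reported singly. That is the natural reading.

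**The case against.** Four points can be made on the other side.

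*The severity rule is an omission in a condensed article.* It gives a response key and a mean and cites a source instrument. Reversing a negatively worded item is routine and may sit in a fuller plan or codebook. This stands in part: those documents are not at hand, and the text nowhere forbids reversal. But the article spells out reversal for two other scales and does not say that severity scoring defers to its source, so a programmer working from it would average the raw items. For the coping pair the defence fails, because the direction is written down.

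*Clear understanding is also keyed as distress.* If it is reported singly, no information is lost and only the label needs care. This stands.

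*The coping pair is a small matter.* It belongs to one arm, applies only to people with a cancer history in a trial that excludes prior melanoma, and enters no MICRA subscale or total. This stands as a limit on importance. The group need not be empty, since the risk score under Randomisation and blinding includes a history of keratinocyte cancer.

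*The SSEAS range is only a label.* It changes no score if the eight items and the 0–4 key are right. But 40 would also be the maximum for ten items scored 0–4, or for eight items scored 1–5, and the document does not show which part is wrong.

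A reader might go further and infer that both scores cancel and that the mediator and psychological-impact aims cannot be answered. The documents do not support that. Severity is attenuated with its order intact, and it is one of many mediators. The psychological-impact aim rests mainly on the MICRA subscales and total, where the positive items are correctly reversed.

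**Conclusion.** The concern holds for two secondary scores. The perceived-severity mean, taken as written, is compressed to one third of its range for consistent respondents. It keeps roughly 33% to 71% of the standardised effect for assumed correlations from 0 to 0.7. That range assumes equal item SDs and the same shift on all three items, and the power figures are illustrative. The coping-pair sum is uninterpretable as written, without any assumption, but only for intervention-arm participants with current or past cancer.

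The SSEAS mismatch of 32 against 40 is a minor inconsistency to be reconciled. Apart from that, the other mediators are unaffected, as are worry, the MHI-5, the MICRA subscales and total, and the primary outcome. The secondary aims are weakened in part; they remain answerable. The correction is worth making because the article commits the final analysis to this plan, and a scoring key changed after the data are seen would be open to the analysis bias that the plan sets out to avoid.

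**What to change.** - **Perceived severity:** state that the easy-to-cure item is scored as 6 minus the response before the mean is taken.
- **Coping pair:** key easier to cope as 5/3/1/0 before summing, so that 0–10 runs from benefit to harm, or report the two items singly.
- **Clear understanding of choices:** report as a single item, labelled so that higher is better. If it is ever combined with regret, reverse it first.
- **SSEAS:** check the item list and key against the questionnaire as fielded, then make the items, key and range agree.

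The cost is a few sentences in the SAP and a few lines of scoring code, dated before the outcome data are examined. No new data are needed. If the scoring code already reverses these items, only the text changes.
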